### Conduct of trial

#### Donor liver selection

Suitable donor liver grafts will be selected from October 2016. Grafts will be retrieved with the intention to transplant and rejected as previously described.

#### Graft inclusion criteria

Rejected donor liver grafts must meet all of the following inclusion criteria to be eligible for inclusion in the VITTAL trial:Liver from a donor primarily accepted with the intention for clinical transplantation;Rejected by all the other UK transplant centres via normal or fast-track sequence;Cold ischaemic time less than 16 hours for DBD and 10 hours for DCD grafts;One of the following parameters which would denote the marginal condition of the liver:Donor risk index greater than 2.0^11^;Graft macrovesicular steatosis greater than 30%;BAR score greater than 9^44^;Donor warm ischaemic time greater than 30 min;Anticipated cold ischaemic time greater than 12 hours for DBD or 8 hours for DCD liver grafts;Suboptimal liver graft perfusion documented by a photo of macroscopic appearance;Donor transaminases (aspartate transaminase (ALT) or alanine transaminase (AST)) above 1000 IU/mL.

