### Adverse events reporting and analysis

The collection and reporting of adverse events (AEs) will be in accordance with the Research Governance Framework for Health and Social Care and the requirements of the National Research Ethics Service (NRES). Definitions of different types of AEs are listed in online supplementary file 1. The reporting period for AEs will commence at visit 1 and end at the 24-month follow-up. The Investigator should assess the seriousness and causality (relatedness) of all AEs experienced by the patient (this should be documented in the source data) with reference to the protocol. This will include abnormal laboratory findings which are reported as clinically significant. All AEs, device deficiencies and adverse device event (ADEs) will be reported using the applicable electronic case report form (eCRF). AEs will be reported in accordance with Clavien-Dindo classification of surgical complications.^40^ Anticipated AEs include those related to any form of major surgery; infection (chest, urine, blood, bile, wound, abdominal), fluid collection (abdominal, pleural), renal dysfunction, cardiac failure, respiratory failure and those related to the disease process and transplantation; early allograft dysfunction, rejection, hospitalisation for pre-existing condition that has not deteriorated, clinically significant abnormal laboratory finding or other abnormal assessments that is associated with the condition being studied (unless judged by the investigator as more severe than expected for the patient’s condition). The investigator will exercise his/her medical judgement in deciding whether an abnormal laboratory finding or other abnormal assessment is clinically significant. However, if in the opinion of the investigator, the frequency or severity of the event is greater than would be expected then it must be reported. Device deficiencies that did not lead to an adverse event but could have led to a medical occurrence if suitable action had not been taken or intervention had not been made or if circumstances had been less fortunate will also be recorded and reported.

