### Those events not being reported

The following are considered routine during or after liver transplantation and will not be reported as AEs.Initial admission to intensive care following liver transplant;Elevation of AST and/or ALT<2000 iu/mL within 48 hours of liver transplant;Transfusion of ≤5 units of packed red cells;Transfusion ≤8 units of fresh frozen plasma;Transfusion ≤2 adult doses of platelets.

In addition to the above, medical and scientific judgement should be exercised in deciding whether expedited reporting is appropriate in other situations, such as important medical events that may not be immediately life threatening or result in death or hospitalisation but may jeopardise the patient or may require intervention. Any death occurring during the protocol defined follow-up period (within 90 days), whether considered device related or not, must be reported as an SAE within 24 hours of the local investigator becoming aware of the event. If a death occurs in a patient receiving a transplant, the cause of death will be investigated and reviewed by the Trial Management Group (TMG) and clinical team caring for the patient. Entry of patients in to the study would be temporarily suspended until these investigations are complete.

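### The donor transaminase criterion and the 48-hour adverse-event exemption are written per mL, so as worded neither limit can separate one case from another

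*Protocol article*

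**What the plan says.** Under Graft inclusion criteria, a rejected liver must meet several conditions, one of which is "One of the following parameters which would denote the marginal condition of the liver". Seven parameters follow, and any one is enough. The last is "Donor transaminases (aspartate transaminase (ALT) or alanine transaminase (AST)) above 1000 IU/mL".

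Under Those events not being reported, the article opens a list of five items with "The following are considered routine during or after liver transplantation and will not be reported as AEs". The second item is "Elevation of AST and/or ALT<2000 iu/mL within 48 hours of liver transplant".

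The section on adverse events reporting and analysis adds a general override: "if in the opinion of the investigator, the frequency or severity of the event is greater than would be expected then it must be reported".

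The article states no other transaminase limit, and nowhere does it give these two limits in another unit. It does not say in which unit the hospital laboratory reports the enzymes.

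**The concern.** Both numbers decide something. The first helps determine which declined livers count as marginal. The article presents clearly defined criteria for discarded organs as a strength of the study, and its Discussion relies on fixed inclusion measures to answer the variation in organ use between centres. The second determines which early enzyme rises enter the adverse-event rates, which are a secondary outcome measure.

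A limit is useful only if some cases fall on each side of it. A cut-off above 1000 presupposes that some donors exceed it, and an exemption below 2000 presupposes that some rises are larger and therefore reportable. If the stated unit puts both limits far beyond any value that can occur, the first never admits a liver and the second never leaves a rise outside the exemption.

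**Working it through.** The article reports no calculation on this point, so there is no figure to reproduce. The check is a unit conversion followed by a comparison with an assumed ceiling.

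**Inputs**
- Donor criterion: above 1000 IU/mL (Graft inclusion criteria).
- Exemption: below 2000 IU/mL, within 48 hours of transplant (Those events not being reported).
- Conversion: 1 L = 1000 mL, so 1 IU/mL = 1000 IU/L.
- Highest attainable serum transaminase: not in the article. Assumed range 10,000 to 100,000 IU/L, that is 10 to 100 IU/mL.

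**Conversion**
- Donor criterion: 1000 IU/mL × 1000 mL/L = 1,000,000 IU/L.
- Exemption: 2000 IU/mL × 1000 mL/L = 2,000,000 IU/L.

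**Ratio of limit to assumed ceiling**

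| Limit | Ceiling 10,000 IU/L | Ceiling 100,000 IU/L |
|---|---|---|
| Donor criterion, 1,000,000 IU/L | 1,000,000 / 10,000 = 100 | 1,000,000 / 100,000 = 10 |
| Exemption, 2,000,000 IU/L | 2,000,000 / 10,000 = 200 | 2,000,000 / 100,000 = 20 |

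The conclusion is the same at both ends of the range. The donor criterion could not be met, and every rise in the 48-hour window would lie below the exemption limit. The ceiling would have to reach 1,000,000 IU/L, ten times the top of the assumed range, before the donor criterion could be met at all.

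**Reach of each limit**
- Eligibility: 1 of 7 alternative routes is closed as written, and 7 − 1 = 6 remain. A liver is affected only if raised transaminases are its sole marginal feature. The article does not say how often that happens.
- Safety reporting: 1 of 5 exempted items is affected, only for the first 48 hours, and subject to the investigator's override quoted above.
- Design: neither limit is an input to the two-stage design for the rescue rate (24 then 29 livers, 53 in all) or to the three-stage design for 90-day survival (3, 11 and 22 transplants), so sample size, alpha and power stay as stated.

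**Enzyme names**

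The donor criterion labels aspartate transaminase as ALT and alanine transaminase as AST. The abbreviations under Table 3 give AST as aspartate transaminase. Because either enzyme satisfies the criterion, the swap does not change which livers qualify.

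**The case against.** The strongest reply is that the article does not contradict itself here. Both limits use the same unit, and no laboratory unit or attainable value is given to set against them. The claim that neither limit can separate cases therefore rests on an assumed ceiling. That is correct, and the conclusion should be stated as conditional. It is not fragile, however, since it holds across a tenfold range with at least a tenfold margin.

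The second reply concerns consequence. A reader might infer that early graft injury would go unreported. The article does not support that. Clinically significant laboratory findings fall within the investigator's assessment of adverse events. Early allograft dysfunction is an anticipated adverse event, and its incidence is part of a secondary objective. Judgement on expedited reporting is required directly after the exemption list. Liver function tests are a secondary outcome measure, and AST is among the scheduled routine blood tests. What is affected is whether an isolated rise in the first 48 hours is labelled an adverse event by the numerical rule. These points stand and limit the weight of the finding. They do not repair the rule, because the override is a fallback to the numerical limit and not a substitute for it.

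A third reply is that clinical staff would probably read both limits in the unit they are used to. That may be so, but it means that the limit applied would differ from the limit published.

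A reader might also infer that the eCRF rejects eligible livers or suppresses reports. The article describes no edit checks and no unit fields, and the full protocol is not shown, so whether the same unit stands in the operational documents is unknown. That harm is possible but not shown.

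**Conclusion.** The point holds in a limited form. Two operational limits are wrong as written. On the assumption that serum transaminases stay at or below 10,000 to 100,000 IU/L, the donor criterion lies 10 to 100 times and the exemption 20 to 200 times beyond any attainable value. One of seven routes to marginal status could then not be met. An isolated enzyme rise in the first 48 hours would escape adverse-event reporting unless the investigator judged it more frequent or severe than expected.

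Nothing stronger follows. It would be wrong to conclude that livers with high enzymes are shut out of the trial, since they may qualify by another route, or that early enzyme data are lost, since they are collected anyway. The primary outcomes and the design figures do not depend on either limit. The matter is of minor severity, but it should be corrected because it sits in an eligibility criterion and a safety-reporting rule and not in background text.

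**What to change.** Confirm the intended figures and unit for both limits against the full protocol and the unit in which the hospital laboratory reports. Correct the two lines so that they agree with each other and with what the trial applies. No threshold is proposed here; the sponsor should state the one that was meant.

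In the same edit, put the enzyme abbreviations in the donor criterion the right way round, which is editorial only. If the eCRF holds either limit, check that it uses the same unit.

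The cost is the correction of two lines and, if applicable, one check of the eCRF. No analysis, sample size or decision rule has to change.

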### Graft exclusion criteria

Livers meeting any of the following criteria would not be suitable for the VITTAL trial:Grafts from patients with active Hepatitis B, C or HIV infection;Livers with macroscopic appearance consistent with cirrhosis;Livers with advanced fibrosis;DCD grafts with donor warm ischaemic time (systolic blood pressure less than 50 mm Hg to aortic perfusion) more than 60 min;Excessive cold ischaemic times (DBD more than 16 hours / DCD more than 10 hours);Paediatric donor (<18 years);ABO (blood group) incompatibility.

### Recipient inclusion criteria

Suitable potential VITTAL graft recipients will be identified during the listing process. Patients will be told that they are potentially suitable to receive a graft from the VITTAL trial and will be given the patient information sheets to read more about the trial. If already listed, potential recipients will be identified on the list, contacted and sent the same documentation. If they wish to take part, a minimum of verbal consent will be taken. Enrolling in the trial will in no way impact on the chance of them receiving a standard ‘transplantable’ graft. Patient’s with all aetiologies of chronic liver disease will be considered for inclusion. Listed patients must meet all of the following inclusion criteria to be eligible for participation in the VITTAL trial:Adult primary liver transplant recipient;Patient listed electively for transplantation;Low to moderate transplant risk candidate, suitable for marginal graft, as assessed by the UHBFT liver transplant listing multidisciplinary team (MDT) meeting (these are usually candidates with low UKELD score, without cardiovascular comorbidities, with good functional and nutrition status, with patent portal vein and with no history of previous major upper abdominal surgery, for example, patients transplanted for liver cancer);There is no lower limit for MELD or UKELD. Upper UKELD is discussed in the exclusion criteria below.

### Recipient exclusion criteria

Subjects who meet any of the following exclusion criteria are excluded from participating in the VITTAL trial:‘High-risk patients’ and recipients not considered suitable for a marginal graft (these are mainly patients with high UKELD score (>62 as per the NHSBT Liver Advisory Group (LAG) criteria for graft sharing in high-risk recipients in the North East of the UK with cardiovascular comorbidities or renal insufficiency, with poor nutrition and performance status or history of major upper abdominal surgery, for example, patients listed for liver retransplantation) (http://www.odt.nhs.uk, search ‘Liver Allocation Policy’);Patients with complete portal vein thrombosis diagnosed prior to the transplantation;Liver retransplantation;Patients with fulminant hepatic failure;Patients undergoing transplantation of more than one organ;Contraindication to magnetic resonance imaging (ie, pacemaker fitted).

### Adverse events reporting and analysis

The collection and reporting of adverse events (AEs) will be in accordance with the Research Governance Framework for Health and Social Care and the requirements of the National Research Ethics Service (NRES). Definitions of different types of AEs are listed in online supplementary file 1. The reporting period for AEs will commence at visit 1 and end at the 24-month follow-up. The Investigator should assess the seriousness and causality (relatedness) of all AEs experienced by the patient (this should be documented in the source data) with reference to the protocol. This will include abnormal laboratory findings which are reported as clinically significant. All AEs, device deficiencies and adverse device event (ADEs) will be reported using the applicable electronic case report form (eCRF). AEs will be reported in accordance with Clavien-Dindo classification of surgical complications.^40^ Anticipated AEs include those related to any form of major surgery; infection (chest, urine, blood, bile, wound, abdominal), fluid collection (abdominal, pleural), renal dysfunction, cardiac failure, respiratory failure and those related to the disease process and transplantation; early allograft dysfunction, rejection, hospitalisation for pre-existing condition that has not deteriorated, clinically significant abnormal laboratory finding or other abnormal assessments that is associated with the condition being studied (unless judged by the investigator as more severe than expected for the patient’s condition). The investigator will exercise his/her medical judgement in deciding whether an abnormal laboratory finding or other abnormal assessment is clinically significant. However, if in the opinion of the investigator, the frequency or severity of the event is greater than would be expected then it must be reported. Device deficiencies that did not lead to an adverse event but could have led to a medical occurrence if suitable action had not been taken or intervention had not been made or if circumstances had been less fortunate will also be recorded and reported.

### Those events not being reported

The following are considered routine during or after liver transplantation and will not be reported as AEs.Initial admission to intensive care following liver transplant;Elevation of AST and/or ALT<2000 iu/mL within 48 hours of liver transplant;Transfusion of ≤5 units of packed red cells;Transfusion ≤8 units of fresh frozen plasma;Transfusion ≤2 adult doses of platelets.

In addition to the above, medical and scientific judgement should be exercised in deciding whether expedited reporting is appropriate in other situations, such as important medical events that may not be immediately life threatening or result in death or hospitalisation but may jeopardise the patient or may require intervention. Any death occurring during the protocol defined follow-up period (within 90 days), whether considered device related or not, must be reported as an SAE within 24 hours of the local investigator becoming aware of the event. If a death occurs in a patient receiving a transplant, the cause of death will be investigated and reviewed by the Trial Management Group (TMG) and clinical team caring for the patient. Entry of patients in to the study would be temporarily suspended until these investigations are complete.

### Study visit overview

The VITTAL trial involves a minimum of four patient visits which all coincide with standard admissions either for surgery or for outpatient follow-up. There are no additional trial-specific visits. The schedule for the study visits and data collection is summarised in table 3. Visit 1 encapsulates admission for transplant and the postoperative period if the transplant proceeds. Visits 2, 3 and 4 are scheduled for 30-day, 90-day and 180-day follow-up, respectively. All patients will undergo MRCP during visit 4 to investigate the occurrence of ischaemic-type biliary lesions which also marks trial end-point. Patients will continue to be followed up at 12 months and 24 months as part of their standard post-transplant care, and data will be collected at these time-points for long-term reporting.

**Table 3 T3:** Patient schedule of events

Patient registration	Screening	Visit 1 Transplant Day 0	Visit 2 Day 30 (+/−3 days)	Visit 3 Day 90 (+3 days)	Visit 4 Day 180 (+30 days)	Extended follow-up 12 months+24 months (+/− 30 days)
Informed consent	X					
Eligibility assessment	X	X				
Patient history	X	X				
Standard routine blood tests*	X	X	X	X	X	X
MELD (automatically calculated)		X				
UKELD (automatically calculated)		X				
Trial-specific additional patient samples blood and urine		X	X	X	X	
PBMC collection		X	X	X	X	
Liver biopsy 4 (see table 2)		X				
Quality of life questionnaire (EQ-5D-5L)		X	X		X	
Patient resource log at visit one discharge		X				
Adverse/Clinical events	X	X	X	X	X	X
Concomitant medications	X	X	X	X	X	X
MRCP					X	

*Standard routine blood tests—FBC, urea, electrolytes, liver function tests, AST, GGT, eGFR, INR.

AST, aspartate transaminase; eGFR, estimated glomerular filtration rate; EQ-5D-5L, EuroQoL 5 Dimensions 5 Levels; FBC, full blood count; GGT, gamma glutamyl transferase; INR, international normalised ratio; MELD, model for end-stage liver disease; MRCP, magnetic resonance cholangiopancreatography; PBMC, peripheral blood mononuclear cell; UKELD, UK end-stage liver disease.

### Storage of samples

Patient blood samples taken as part of their standard of care will be processed and stored according to UHBFT procedures. Perfusate, patient serum, plasma, urine samples and mononuclear cell preparations collected during visits 1–4 will be stored frozen in 0.5–1.0 mL aliquots at – 80°C at the Institute of Biomedical Research, University of Birmingham. Liver biopsy tissue specimens will be collected and the formalin fixed paraffin embedded segments will be processed by staff in the department of cellular pathology at UHBFT. After sectioning and staining, tissue blocks will be stored at the Institute of Biomedical Research. All samples will be collected in accordance with national regulations and requirements including standard operating procedures for logistics and infrastructure. Samples will be taken in appropriately licensed premises, stored and transported in accordance with the Human Tissue Authority guidelines and trust policies.

### Data handling, quality assurance, record keeping and retention

Data will be managed according to the standard operating procedures of the Cancer Research UK Clinical Trials Unit (CRCTU) at the University of Birmingham, UK. The CRCTU is fully compliant with the Data Protection Act 1998 and the Guidelines for Good Clinical Practice. The CRCTU will monitor the trial and provide annual reports to the MHRA. The trial is registered with the Data Protection Act website at the University of Birmingham. Donor and patient details will be kept anonymous (specific study identification codes will be used for each study donor). Anonymised donor data will be used in future publications arising from the study. Patients will be identified using only their unique registration number, patient initials on the case report form and correspondence between the trials office and the participating site. In addition, the patients are requested to give permission for the trials office to be sent a copy of their signed Informed consent form which will not be anonymised. This will be used to perform in-house monitoring of the consent process. Identifiable data will only be made available to authorised staff of the study sponsor, its authorised representatives and regulatory authorities. All patients will be consented specifically to enable data to be shared as detailed above. Confidentiality will otherwise be maintained throughout the trial and thereafter and data will be anonymised. On completion of the trial, data will be transferred to a secure archiving facility at the University of Birmingham, where data will be held for a minimum of 15 years and then destroyed.

### Electronic case report forms

Electronic case report forms (ECRFs) have been designed to capture as much, donor, perfusion and patient data as possible and feasible. The liver registration form and donor history form detail all that is relevant regarding the quality of the graft itself. The perfusion form enables collection of the perfusion parameters, biochemical data and the outcome of the perfusion. The patient registration and visit 1 forms will capture the demographics of the recipient as well as track the operative and postoperative course. Visits 2–4 are for patient follow-up.

### Trial organisational structure

The University of Birmingham will act as single sponsor this single-centre study. The trial is being conducted under the auspices of the CRCTU, The University of Birmingham according to their local procedures. The TMG will be responsible for the day-to-day running and management of the trial. Members of the TMG include the chief investigator, coinvestigators, project manager, trial management team leader, senior trial coordinator, trial coordinator, lead trial statistician and trial statistician. The TMG will have regular meetings during recruitment. The DMC will consist of independent clinicians [name], [name] and [name] as well as an independent statistician, [name]. Data analyses will be supplied in confidence to the independent DMC, which will be asked to give advice on whether the accumulated data from the trial, together with the results from other relevant research, justifies the continuing recruitment of further patients. The DMC will operate in accordance with a trial specific charter based on the template created by the Damocles Group. The DMC will meet at two scheduled time-points after the interim analyses as previously described (figure 2). An emergency meeting may also be convened if a safety issue is identified. The DMC will report directly to both the VITTAL Trial Management Group (chief investigator) who will convey the findings of the DMC to the trial steering group and funders/sponsor as appropriate or when specifically requested by these parties.

